### Primary Outcomes

The primary outcome is live birth (Table 3). Live birth is defined as the birth of at least one living fetus, and the live birth rate is calculated as live birth per embryo transfer.

**Table 3 T3:** Overview of follow-up during pregnancy and time of assessment.

**Time**	**Case report form**
Early pregnancy ( ≤ 12 weeks)	1. Follow-up pregnancy outcome of the pregnant women live birth/premature birth/abortion/ stillbirth; 2. Whether there are symptoms of fever, cough, night sweat, or blood in sputum; If yes, a blood routine test, chest X-ray imaging, and lung CT examination will be performed. If pulmonary tuberculosis is diagnosed, it will be confirmed by clinical diagnosis/microbiology; 3. Follow-up of the newborn: birth weight and health status
Second trimester (13–27 weeks)	
Late pregnancy (≥28 weeks)	
Three months after delivery	

*CT, computed tomography*.

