## Methods and Analyses

### Study Design

This is a prospective cohort study of infertile patients who will undergo IVF-ET from January 1, 2022, to December 30, 2024, at Peking University Third Hospital. According to the sample size calculation, ~1,200 participants will be enrolled. The inclusion criterion is untreated PTB on CXR. The exclusion criteria are (1) active TB, (2) a previous diagnosis of TB, (3) TB other than PTB (e.g., reproductive system TB, renal TB, lymphatic TB), (4) the presence of central nervous system diseases, cancer, or AIDS, (5) long-term oral corticosteroids, immunosuppressants, and inhaled corticosteroid therapy, which may increase the risk of TB, and (6) patients who lack decisional capacity or who cannot guarantee their participation until the end of the study (Table 1). Participants will be divided into IGRA-positive and -negative groups, and the pregnancy outcomes will be followed during pregnancy. We will investigate whether LTBI (positive IGRA) in patients with untreated prior PTB affects the pregnancy outcomes (Figure 1).

**Table 1 T1:** The inclusion and exclusion criteria for selecting the study participants.

**Primary inclusion criteria**	**Primary exclusion criteria**
• Age 18–45 years • Untreated prior PTB based on chest X-ray imaging findings	• Active TB•History of treated previous • TB other than PTB (e.g., reproductive system TB, renal TB, and lymphatic TB) • The presence of central nervous system diseases, cancer, or AIDS • Long-term oral corticosteroids, immunosuppressants, and inhaled corticosteroid therapy • Patients who lack decisional capacity or who cannot guarantee their participation until the end of the study

*AIDS, acquired immunodeficiency syndrome; PTB, pulmonary tuberculosis*.

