### Sample Size Calculations

We explored the effect of positive IGRA on pregnancy outcomes after adjustment for age, BMI, infertility causes, COH protocol, endometrial thickness, and number of good-quality embryos. There were 19 variables (including the dummy variables) in the logistic regression model. Considering the sample size requirement of multivariate logistic regression, 190 live birth events are required based on the 10 events per variable (including dummy variables) rule (25). Assuming that the live birth rate is 30% and the embryo transplantation rate is 53% (13, 23), a sample of 1,200 participants is required.

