### Statistical Analysis

Statistical analysis will be performed using SPSS version 25 (IBM Corp., Armonk, NY). Continuous data will be expressed as means (± standard deviation), with independent sample *t*-tests or the Mann-Whitney U test for between-group differences. Categorical variables such as causes of infertility and COH protocol will be represented as frequency and percentage and analyzed using the Chi-square test.

The pregnancy outcomes of the IGRA-positive and IGRA-negative groups will be compared using the Chi-square test. We will use multivariate logistic regression to adjust for the effect of baseline characteristics. Adjusted odds ratios, 95% confidence intervals, and *p*-values will be reported. A two-tailed *p*-value < 0.05 will be considered statistically significant.

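### The primary outcome, live birth per embryo transfer, conditions on an event after IGRA grouping and leaves about 47% of enrolled women out of the comparison

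*Protocol article*

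**What the plan says.** - **Question (Study Design).** "We will investigate whether LTBI (positive IGRA) in patients with untreated prior PTB affects the pregnancy outcomes". The population is the enrolled cohort: 1,200 infertile women with untreated prior pulmonary TB on chest X-ray.
- **Exposure (LTBI Screening, Introduction).** Women are put into two groups by their IGRA result. The Introduction speaks of latent infection found before IVF-ET.
- **Primary outcome (Primary Outcomes).** The event is any birth with a living child, and its denominator is fixed in the same sentence: "the live birth rate is calculated as live birth per embryo transfer". No rate per enrolled woman or per started cycle is given anywhere.
- **Planning figures (Sample Size Calculations).** "There were 19 variables (including the dummy variables) in the logistic regression model"; "190 live birth events are required based on the 10 events per variable (including dummy variables) rule"; "Assuming that the live birth rate is 30% and the embryo transplantation rate is 53% (13, 23), a sample of 1,200 participants is required".
- **Analysis (Statistical Analysis).** "The pregnancy outcomes of the IGRA-positive and IGRA-negative groups will be compared using the Chi-square test", followed by multivariate logistic regression.
- **Treatment path (IVF-ET Protocols).** Every eligible participant is said to go through stimulation, retrieval, fertilization and transfer. One planned transfer of one or two embryos is described, on day 3 or 5 after retrieval. Repeat cycles and frozen transfers are not mentioned.

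**The concern.** Whether a woman reaches transfer is decided after her IGRA status is fixed. It depends on how her ovaries respond, whether usable embryos result and whether the endometrium is suitable. The Introduction names endometrial and ovarian involvement as ways in which TB impairs fertility, and Secondary Outcomes lists retrieved oocytes and high-quality embryo rate. The denominator of the primary outcome therefore lies on the hypothesised causal path.

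Two consequences follow. First, an effect of latent infection that works by preventing transfer cannot appear in the primary result. Second, the women who do reach transfer may differ between the groups in unmeasured prognosis. Logistic adjustment among transferred women does not bring the others back.

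Strengths and Limitations says the results will serve as strong evidence on preventive treatment and inform guidelines. A finding of no difference that reflects only the choice of denominator would matter there.

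**Working it through.** **Inputs from the protocol article.** 19 model variables, 10 events per variable, 30% live birth rate, 53% transfer rate, N = 1,200 (Sample Size Calculations); 75.5% IGRA positivity (Introduction, an unpublished figure, used here only to split the groups).

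**1. Reproduce the stated sample size.** Events needed = 19 × 10 = 190. N = 190 / (0.30 × 0.53) = 190 / 0.159 = 1,194.97, so 1,195, against about 1,200 stated. It reproduces. Without the 53% factor, N = 190 / 0.30 = 633.3, so 634. Hence the 53% is a rate per participant, the 30% is a rate per transfer, and the formula counts at most one transfer per woman.

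**2. Who is left in the primary comparison.**
- Women with a counted transfer: 1,200 × 0.53 = 636.
- Women without: 1,200 − 636 = 564 (47%).
- Expected live births: 636 × 0.30 = 190.8.
- Live birth per enrolled woman: 0.53 × 0.30 = 15.9%; 1,200 × 0.159 = 190.8, the same events.

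**3. What the denominator can hide.** The protocol gives no transfer rates by group, so these are assumed. With 75.5% positive, each pair averages about 53% (for example 0.755 × 50.7% + 0.245 × 60% = 53.0%).

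| Transfer rate, IGRA+ / IGRA− | Live birth per transfer, IGRA+ / IGRA− | Live birth per woman, IGRA+ / IGRA− | Per-woman ratio |
|---|---|---|---|
| 51.0% / 59.2% | 30% / 30% | 15.3% / 17.8% | RR 0.86, OR 0.84 |
| 50.7% / 60.0% | 30% / 30% | 15.2% / 18.0% | OR 0.82 |
| 50.0% / 62.25% | 30% / 30% | 15.0% / 18.7% | RR 0.80, OR 0.77 |
| 50.0% / 62.25% | 31% / 28% | 15.5% / 17.4% | RR 0.89, OR 0.87 |

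For the second row, the odds are 0.1521/0.8479 = 0.179 and 0.18/0.82 = 0.220, with ratio 0.82. In the first three rows the planned analysis shows no difference. In the fourth it favours the IGRA-positive group while the per-woman rate favours the IGRA-negative group.

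**4. What the change does to precision and power.** The groups are 906 and 294 women, or about 480 and 156 transfers at a common 53%.
- SE of the log OR under no effect, √[1/(n₁p(1−p)) + 1/(n₂p(1−p))]: 0.201 per transfer (p = 0.30) and 0.184 per woman (p = 0.159). These are different estimands, so the smaller SE is not by itself a gain.
- Suppose transfer is 53% in both groups and latent infection acts only afterwards, with 30% against 20% per transfer. Per woman this is 15.9% against 10.6%. The log OR shrinks from −0.539 to −0.467, and power (two-sided 0.05, unadjusted) falls from about 73% to about 68%. At 30% against 22% it falls from about 53% to about 47%.
- For the 18.0% against 15.2% example, per-woman power is only about 21%.

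**The case against.** Live birth per transfer is a coherent measure of what happens after transfer, and the protocol keeps oocyte number and high-quality embryo rate as secondary outcomes, so some earlier effects would still be visible. This stands, and the outcome is not invalid. It is incomplete for the question in Study Design, which concerns the enrolled women.

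The 47% is derived from a planning assumption. The protocol does not say whether these women never have a transfer or only have none in the counted cycle. This also stands. If every eligible woman did reach transfer, as IVF-ET Protocols says, the selection would vanish, but the 53% behind the sample size would then be wrong.

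The per-woman outcome costs some power if latent infection acts only after transfer, and it would probably miss the illustrated effect too. Both are true. The change corrects what is estimated; it does not rescue power.

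Two stronger readings are tempting and are not supported:
- **That the plan counts women more than once and so inflates the type I error.** The text does not restrict the outcome to one transfer per woman, and the planned tests assume independence. But only one planned transfer is described, and the sample size uses at most one. With an assumed 1.3 to 2 transfers per woman and an intraclass correlation of 0.1 to 0.2, the design effect 1 + (m − 1) × ICC is about 1.03 to 1.20. The documents give neither figure. Repeat counting is an open possibility to close, not a stated plan.
- **That the bias runs towards no effect.** The direction depends on group-specific transfer rates and on prognosis among women reaching transfer, neither of which is given. The fourth row of the table shows a reversal instead.

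**Conclusion.** The concern holds for the denominator. The primary rate is conditional on a post-exposure event that the protocol's own reasoning places on the causal path, and by its own planning figure about 564 of 1,200 women (47%) are left out. Followed as written, the plan can report no difference when latent infection lowers a woman's chance of a live birth. In the illustrations the hidden per-woman OR is 0.77 to 0.84; those sizes rest on assumed transfer rates by group and on 75.5% IGRA positivity. Whether such an effect exists, and which way selection would push the result, cannot be told from the document. The sample size arithmetic is sound on its own terms and is not at issue.

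**What to change.** 1. Define the primary outcome as live birth per enrolled woman (or per woman starting her first cycle after IGRA) within a fixed window, with no transfer counted as no live birth and one observation per woman.
2. Keep live birth per transfer as a secondary outcome, limited to the first transfer or analysed with cluster-robust standard errors.
3. Reconcile the statement in IVF-ET Protocols that all eligible participants undergo transfer with the 53% in Sample Size Calculations, and say what the 53% refers to.
4. Check the listed adjusters. Endometrial thickness and number of good-quality embryos arise during the cycle, so requiring them in the per-woman model could drop the same women again.

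**Cost.** New outcome wording and a registry update; the denominator is simply the enrolled cohort. Expected live births stay at 190.8, so the 190-event target and N = 1,200 stand. The headline rate falls from about 30% to about 16%, and power is slightly lower if latent infection acts only after transfer (about 73% to 68% in the 30% against 20% case).

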### Secondary Outcomes

The secondary outcomes include the numbers of retrieved oocytes, high-quality embryo rate, clinical pregnancy, number of active TB cases during pregnancy, and miscarriage (Table 3). Clinical pregnancy is determined upon observation of a gestational sac on ultrasonography. Miscarriage is defined as pregnancy loss before 28 weeks of gestation. The clinical pregnancy and miscarriage rates have been calculated as described earlier in this article (13, 23).

### Sample Size Calculations

We explored the effect of positive IGRA on pregnancy outcomes after adjustment for age, BMI, infertility causes, COH protocol, endometrial thickness, and number of good-quality embryos. There were 19 variables (including the dummy variables) in the logistic regression model. Considering the sample size requirement of multivariate logistic regression, 190 live birth events are required based on the 10 events per variable (including dummy variables) rule (25). Assuming that the live birth rate is 30% and the embryo transplantation rate is 53% (13, 23), a sample of 1,200 participants is required.

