## Introduction

Tuberculosis (TB), an infectious disease caused by *Mycobacterium tuberculosis*, seriously affects human health (1, 2). According to a report by the World Health Organization (WHO) in 2020, the global TB incidence rate is ~130 per 100,000 (1). TB may affect the reproductive ability of women and is a common cause of infertility due to blockage of the fallopian tubes or through the involvement of endometrium or ovarian functions (3, 4). Early identification of active TB cases and active anti-TB treatment are essential. However, the onset of TB is insidious, even without symptoms, and some patients may present with “infertility.” *In vitro* fertilization and embryo transfer (IVF-ET) remains the most effective method of treating associated infertility (5).

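### The only adjusted model described conditions on two IVF-cycle variables that follow the exposure, so its odds ratio omits any LTBI effect acting through them and is not the total effect

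*Protocol article*

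**What the plan says.** - Sample Size Calculations: the effect of a positive IGRA on pregnancy outcomes is estimated "after adjustment for age, BMI, infertility causes, COH protocol, endometrial thickness, and number of good-quality embryos". The section adds: "There were 19 variables (including the dummy variables) in the logistic regression model". The sample size is built on this model.
- Statistical Analysis: IGRA groups are compared by an unadjusted chi-square test, and the plan then uses "multivariate logistic regression to adjust for the effect of baseline characteristics". No covariates are listed there.
- Table 2 is titled as baseline characteristics. Its IVF-ET data row contains the number of good-quality embryos and endometrial thickness, beside retrieved oocytes and embryos transferred.
- Introduction: TB is said to cause infertility by tubal blockage or "through the involvement of endometrium or ovarian functions".
- Secondary Outcomes: these include "the numbers of retrieved oocytes, high-quality embryo rate, clinical pregnancy".
- Introduction, Study Design and Discussion: the question is whether LTBI, shown by a positive IGRA, affects pregnancy outcomes after IVF-ET. The answer is meant to inform decisions on preventive treatment. Nowhere is a direct effect, net of embryo and endometrial changes, named as the target.

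**The concern.** A good-quality embryo exists only after stimulation, retrieval and fertilization, and endometrial thickness is recorded as cycle data. Both come after the infection that IGRA is meant to detect. If LTBI lowers embryo yield or impairs the endometrium, these variables lie on the path from exposure to live birth, and holding them fixed blocks that path. If embryo yield and live birth also share causes outside the model, such as ovarian reserve, conditioning on embryo yield can bias the IGRA odds ratio in either direction.

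The study asks about the overall effect, because a decision on preventive treatment before IVF needs every route counted. In an observational cohort the adjusted odds ratio is likely to carry the inference, and this is the only adjusted model described.

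**Working it through.** **1. The plan's own figure.** Inputs from Sample Size Calculations: 19 terms, 10 events per term, live birth rate 30%, transfer rate 53%.

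- Events: 19 × 10 = 190.
- Women: 190 / (0.30 × 0.53) = 190 / 0.159 = 1,194.97, so 1,195. This agrees with the stated 1,200.
- Expected at 1,200: 1,200 × 0.53 = 636 transfers; 636 × 0.30 = 190.8 live births; 190.8 / 19 = 10.0 events per term.

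The sample size reproduces and is not the problem.

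**2. Place of each covariate relative to the exposure.**

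- Age, BMI, infertility causes: known before the cycle.
- COH protocol: chosen after infection status is established, before the cycle's results. Its place is arguable.
- Endometrial thickness and number of good-quality embryos: cycle results, hence after the exposure. The endometrium and ovarian function are routes named in the Introduction, and a closely related embryo measure is a secondary outcome.

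**3. Possible size of the loss (illustration; only the IGRA rate comes from the documents).** Simulation of 1,000,000 records per scenario:

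- 75.5% IGRA-positive (the unpublished rate quoted in the Introduction) and about 31% live birth.
- Two mediators, each with log-odds 0.4 per SD.
- Log-odds effect of LTBI −0.5, of which a share *s* runs through the mediators: each is shifted by *s* × (−0.5) / (2 × 0.4) SD, and the direct part is (1 − *s*) × (−0.5).

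The adjusted model should return about exp[−0.5 × (1 − *s*)].

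| Share mediated | OR without mediators | OR adjusted for both | exp[−0.5(1 − s)] |
|---|---|---|---|
| 0% | 0.62 | 0.60 | 0.61 |
| 25% | 0.63 | 0.69 | 0.69 |
| 50% | 0.62 | 0.78 | 0.78 |
| 75% | 0.63 | 0.89 | 0.88 |
| 100% | 0.62 | 1.00 | 1.00 |

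The small gap at 0% is non-collapsibility of the odds ratio, not bias. The simulation contains no unmeasured common causes, so it shows only the blocking of the path.

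For scale, with 636 transfers split 75.5 : 24.5, an overall rate of 30% and two-sided 5%, an unadjusted comparison has power of about 65% for a 10-point difference (OR 0.63) and 22% for a 5-point difference (OR 0.79). A shift from 0.62 to 0.78 could therefore decide whether an effect is seen.

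**4. Sample size after the change.** Assuming each cycle variable takes one term, 17 remain: 170 / 0.159 gives 1,070 women. If together they take 3 or 4 terms, the figure is 160 / 0.159, or 1,007, or 150 / 0.159, or 944. At 1,200 women, 190.8 / 17 = 11.2 events per term.

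**5. Room for replacements within 19 terms.** AMH, FSH, antral follicle count, infertility duration and smoking need five terms at one each. With COH protocol kept, 17 + 5 = 22 terms, or 190.8 / 22 = 8.7 events per term, which breaks the plan's own rule; only two of the five fit. Table 2 lists six COH categories, so five dummies if all are used. With COH protocol moved to a sensitivity model, 17 − 5 + 5 = 17 terms.

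**The case against.** Several counter-arguments have force.

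- **A reader might infer that the adjustment removes the LTBI effect, or that a real effect would be reported as null.** The documents do not support this. Only the share acting through these two variables is blocked; effects through implantation, miscarriage or active TB in pregnancy remain. A null follows only if the whole effect is mediated, and in the illustration that row is 1.00 by construction.
- **A reader might take it as established that LTBI alters these variables.** It is not. The Introduction speaks of TB, not LTBI, and the cohort excludes active TB and reproductive-system TB, with endometrial biopsy among the checks for active disease. Mediation is plausible, not shown.
- **A reader might see a flat contradiction with the statement that adjustment is for baseline characteristics.** Table 2 places both variables under that title, so by the article's own usage they are baseline. This is a mislabel.
- **Other analyses keep the mediated part.** The chi-square test does, and oocyte and embryo outcomes are examined directly. But the chi-square test controls no confounding, so it cannot replace a properly adjusted total-effect estimate.
- **The covariate list stands only in the sample-size section, in the past tense, and high-quality embryo rate is not identical to number of good-quality embryos.** Both are true. The list nevertheless fixes the 19 terms from which 1,200 was derived, and the two embryo measures are closely related.

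**Conclusion.** The point holds in a limited form. The one adjusted model described conditions on two post-exposure cycle variables that the protocol's own reasoning makes plausible routes to live birth. Its odds ratio omits any LTBI effect through them and may carry bias of unknown direction from unmeasured common causes. It therefore does not answer the total-effect question.

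The size of the loss cannot be derived from the documents. It could be nil if LTBI affects neither variable, and complete if it acts only through them. The illustrated range of 0.69 to 1.00 against 0.62 rests on assumed effect sizes and predicts nothing about this cohort. The planned 1,200 is unaffected.

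**What to change.** 1. In Statistical Analysis, name a main adjusted model with pre-cycle covariates only: age, BMI, infertility causes, and already collected baseline items such as AMH, FSH, antral follicle count, infertility duration and smoking, chosen in advance within the 19-term budget. The ovarian-reserve measures matter most, since they bear on the common causes of embryo yield and live birth.
2. Justify COH protocol as a covariate, or move it to a sensitivity model.
3. Report the model with endometrial thickness and number of good-quality embryos as a secondary direct-effect analysis, so labelled, with its assumption of no unmeasured mediator–outcome confounding stated.
4. Retitle or split Table 2 so that cycle results are not called baseline, and align Sample Size Calculations with Statistical Analysis.
5. State that live birth per embryo transfer still conditions on reaching transfer, itself a post-exposure event: at a 53% transfer rate, 1,200 × 0.47 = 564 enrolled women would not contribute. Dropping the two covariates does not cure this.

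Cost: a few sentences, no new data and no extra recruitment. The main model loses two likely predictors of live birth and so explains slightly less outcome variation.

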### Procedures

Infertile patients who will undergo IVF-ET at the Center for Reproductive Medicine of Peking University Third Hospital will be screened. According to the Code of Practice for Assisted Reproductive Technology developed by the Ministry of Health of the People's Republic of China, all patients will undergo routine CXR examination before IVF-ET (20). Patients with abnormal chest images will be referred to the respiratory clinic for consultation, and those with chest imaging abnormalities consistent with prior PTB will be enrolled. Active TB cases will be excluded based on the clinical assessment (contact history, respiratory symptoms related to TB, physical examination), CXR, microbiological studies of sputum/respiratory samples, and endometrial biopsy findings. Moreover, among those with prior PTB based on CXR findings, patients will be excluded if they have a past history of treatment for active TB, and only those with untreated prior PTB will be enrolled. A total of 1,200 infertile patients with untreated prior PTB on CXR will be enrolled.

Participants' baseline characteristics (demographics, clinical characteristics, IVF-ET treatment) will be obtained from the case registration research database, including age, body mass index (BMI), infertility years, causes of infertility, and the controlled ovarian hyperstimulation (COH) protocol. Baseline levels of hormones will also be recorded, including follicle-stimulating hormone (FSH), luteinizing hormone (LH), estradiol (E2), progesterone (P), prolactin, testosterone (T), androstenedione (A), and anti-Müllerian hormone (AMH), and antral follicle count. Follicles after oocyte promotion, hormone levels (FSH, LH, E2, and P) on human chorionic gonadotropin (HCG) day, and B-ultrasound findings, such as a gestational sac and endometrial thickness, will also be recorded (Table 2).

**Table 2 T2:** Baseline characteristics of the participants.

**General information**	**Age, race, body mass index, smoking, glucose**
Medical history	Primary infertility/secondary infertility; Infertility duration; Cause of infertility Male factors (oligospermia/asthenospermia/other male factors) Female factors (fallopian tube factor/polycystic ovary syndrome/endometriosis/other female factors) Unexplained infertility COH protocol Ultralong GnRH agonist; Short GnRH agonist; GnRH antagonist; Microsimulation cycle; Long GnRH agonist; Natural or other

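### The only itemised adjustment set omits recorded pre-stimulation factors and includes two in-cycle variables, leaving avoidable potential confounding in the adjusted odds ratio

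*Protocol article*

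**What the plan says.** Sample Size Calculations describes a logistic model for the effect of a positive IGRA with "adjustment for age, BMI, infertility causes, COH protocol, endometrial thickness, and number of good-quality embryos". It adds: "There were 19 variables (including the dummy variables) in the logistic regression model". That count sets the event target ("190 live birth events are required based on the 10 events per variable (including dummy variables) rule") and, through it, the enrolment of 1,200.

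Statistical Analysis gives no list: "We will use multivariate logistic regression to adjust for the effect of baseline characteristics". For continuous data it names only t-tests or the Mann-Whitney test.

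Procedures and Table 2 record more than the model uses. They include "anti-Müllerian hormone (AMH), and antral follicle count", "Primary infertility/secondary infertility; Infertility duration", and smoking. Table 2 is headed as baseline characteristics, yet it also holds endometrial thickness and the number of good-quality embryos, which arise during the IVF cycle. Secondary Outcomes includes the high-quality embryo rate and the number of retrieved oocytes.

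**The concern.** Women are grouped by a test result, not by randomisation, so the adjusted odds ratio has to carry the comparison. Strengths and Limitations leans on it heavily, claiming stronger evidence for causality and strong evidence for preventive treatment.

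The listed model has two weaknesses for that purpose:

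- It leaves out five recorded factors that could predict live birth and could differ by IGRA status. Any such difference that age, BMI, infertility cause and COH protocol do not absorb would stay in the estimate.
- It adjusts for two variables measured after the exposure. The Introduction says TB may impair fertility through the endometrium or ovarian function. Endometrial thickness and embryo number may therefore be part of the effect being sought, and conditioning on them could remove that part. Embryo quality is itself a secondary outcome.

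For oocyte number, the only comparison stated is unadjusted, although ovarian reserve and other baseline predictors are recorded.

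**Working it through.** **1. The plan's own figure.** Inputs from Sample Size Calculations: 19 terms, 10 events per term, live birth 30%, embryo transplantation 53%.

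- Events: 19 × 10 = 190.
- N: 190 / (0.30 × 0.53) = 190 / 0.159 = 1,195, stated as 1,200. This reproduces.
- At N = 1,200: 1,200 × 0.53 = 636 women with transfer, and 636 × 0.30 = 190.8 live births.

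**2. Is there room in the 19 terms for the omitted factors?** Table 2 shows 8 infertility-cause levels and 6 COH levels. With IGRA, age, BMI, endometrial thickness and embryo number as single terms, 5 + 8 + 6 = 19. This count drops no reference levels and is an inference from Table 2, not a statement in the article. If it is right, none of the five factors is in the model that sizes the study.

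**3. Standard error of the log odds ratio.** With the 75.5% IGRA positivity quoted in the Introduction, the 636 women split into about 480 and 156. With 30% live birth in both groups:

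SE = √[1/(480 × 0.21) + 1/(156 × 0.21)] = √(0.0099 + 0.0305) = 0.20.

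**4. Possible bias from one omitted factor.** The documents give neither the strength of these factors nor their imbalance by IGRA status, so both are assumed. With no true IGRA effect, the spurious odds ratio is approximately exp(−imbalance × ln OR per SD). The table gives the values from numerical integration, for the case where IGRA-positive women are worse off on the factor:

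| OR per SD | 0 SD | 0.1 SD | 0.2 SD | 0.3 SD |
|---|---|---|---|---|
| 1.2 | 1.00 | 0.982 | 0.964 | 0.947 |
| 1.5 | 1.00 | 0.962 | 0.925 | 0.889 |

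Wherever there is an imbalance, this is between |ln 0.982| / 0.20 = 0.1 and |ln 0.889| / 0.20 = 0.6 standard errors. An imbalance in the other direction would push the odds ratio above 1. The imbalance that matters is what remains after the listed covariates, which may be smaller.

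**5. Does adding a prognostic factor sharpen the primary estimate?** Simulation used 1,500 data sets of 636 women, an assumed true odds ratio of 0.6, and a covariate unrelated to IGRA:

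| Covariate OR per SD | SE without → with | Power without → with |
|---|---|---|
| 1.2 | 0.194 → 0.195 | 74% → 74% |
| 1.5 | 0.194 → 0.198 | 70% → 72% |
| 2.0 | 0.192 → 0.203 | 67% → 71% |

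The standard error does not fall. The small power gain arises because the conditional odds ratio lies further from 1.

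**6. Terms after the change** (one term per added factor, an assumption).

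- Primary model: 19 − 2 + 3 = 20 terms; 190 / 20 = 9.5 events per variable. Keeping strictly to 10 would need 200 / 0.159 = 1,258 women.
- Sensitivity model with AMH and antral follicle count: 22 terms; 190 / 22 = 8.6. Keeping strictly to 10 would need 220 / 0.159 = 1,384 women.
- If the 19 does count every level and reference levels are dropped, the current model has 17 terms. The primary model would then have 17 − 2 + 3 = 18, and 190 / 18 = 10.6.

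**The case against.** The strongest reply is that the list stands in the sample size section, in the past tense, and serves to count terms. Statistical Analysis refers to baseline characteristics generally, Table 2 carries that label, and a final covariate list is commonly left to an analysis plan. This stands in part: the final model is ambiguous, and a reader should not infer that the five factors will certainly be left out, or that the plan breaks a promise to adjust for everything in Table 2. But this is the only itemised model and it fixes N. A broader reading would not fit the 19 terms, so the two sections need one list on either reading.

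Second, confounding also needs an association with IGRA status, and the documents show none. That stands. The inputs in the bias table are assumptions, and at zero imbalance there is no bias. A reader might infer that the primary result is biased; the documents do not support that.

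Third, a reader might infer that the omission adds noise to the primary analysis. It does not do so in the sense of a wider standard error, as the simulation shows. The precision argument applies only to oocyte number, where adjustment for predictors reduces residual variation.

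Fourth, if TB acts through ovarian function, AMH and antral follicle count may themselves be mediators. This stands, and is why they should not enter the primary model. On the same account, infection could precede and prolong infertility, so infertility type and duration are not wholly exempt, although they are fixed before the cycle starts. Smoking is clear of the objection.

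**Conclusion.** The point holds as a weakness in a stated choice of covariates: recorded pre-cycle factors are left out while two post-exposure variables are adjusted for. The consequence is avoidable potential confounding, not demonstrated bias. On the assumed inputs one factor would shift the odds ratio to about 0.98 to 0.89, at most about 0.6 standard errors, before allowing for what age and the other listed covariates already remove. Several factors could add up or cancel. The effect of conditioning on the two in-cycle variables was not quantified; it depends on how far LTBI acts through them, which the documents do not say. The change is worth making because the data are already collected and the comparison is meant to inform treatment decisions.

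**What to change.** - State one itemised primary model, identical in Sample Size Calculations and Statistical Analysis: IGRA status, age, BMI, infertility causes, COH protocol, smoking, primary or secondary infertility, and infertility duration.
- Move endometrial thickness and number of good-quality embryos to a secondary model, described as a mediation analysis.
- Report a sensitivity model that adds AMH and antral follicle count to the primary set, and say that these may be confounders or mediators.
- Compare the number of retrieved oocytes by regression on the same baseline set, alongside the unadjusted test.

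The cost is wording and a few extra model runs on data already planned. The net increase is about one term in the primary model, giving about 9.5 events per variable, and about 8.6 in the sensitivity model. Both are slightly below the plan's own rule of 10. The sample size section should restate these figures; a shortfall of this size does not justify enrolling more women.
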